### Strategies to improve adherence to interventions {11c}

No strategies for intervention adherence are necessary, as the intervention is administered at a single time point during surgery.

### Relevant concomitant care permitted or prohibited during the trial {11d}

All other forms of treatment are permitted; however, patients are not allowed to participate in other clinical studies with investigational drugs or devices.

### Provisions for post-trial care {30}

In accordance with the Belgian Law relating to experiments on human persons (May 7, 2004) the Sponsor shall assume, even without fault, the responsibility of any damages incurred by a study patient and linked directly or indirectly to the participation to the study and shall provide compensation therefore through its insurance.

### Outcomes {12}

The primary end point is the success rate of both techniques at 3 months postoperative, which means the absence of CSF leak that needs surgical revision or any other intervention e.g., lumbar drainage, repeat imaging, or longer hospitalization. Success rate in both groups will be reported in proportions with a 95% confidence interval.

Secondary endpoints include identification of potential risk factors for reconstruction failure, assessment of potential interference of reconstruction material with post-operative imaging, analysis of the effect of the treatment on quality of life (QoL), and post-operative rhinological symptoms. Rhinological symptoms are assessed based on specific validated questionnaires, i.e. visual analog scale (VAS) (for runny nose, nasal itches, sneezing, nasal congestion, facial pain, headache, loss of smell), Sino-Nasal Outcome Test-22 (SNOT-22) and Skull Base Inventory (SBI).

The outcomes will be assessed at six study visits within a time frame of 1 year (Table 2), and a comparison will be made between the two groups considering the change to baseline (preoperative visit). Data will be presented as mean and standard deviation or median and interquartile range for continuous variables (including VAS score, SBI score, SNOT-22 score) or as proportions with 95% confidence intervals for categorical variables (intraoperative leak, complications, surgical indication, or type of tumor).

**Table 2 Tab2:** Outcome assessment

**Procedure**	**Visit 1** *Screening*	**Visit 2** *Allocation*	**Visit 3** *FU1*^a^	**Visit 4** *FU 2*^b^	**Visit 5** *FU 3*^c^	**Visit 6** *FU 4*^d^

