#### Screening

At the day of hospital admission (usually 1 day before surgery), informed consent is obtained and eligibility criteria are checked. A medical history questionnaire with identification of potential risk factors for reconstruction failure and post-operative CSF leaks will be filled out. The patient will be asked to complete nasal symptom scoring (SNOT-22, SBI, VAS scoring) and EQ-5D-3L questionnaires to assess the quality of life. Pre-operative MR images will be evaluated.

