### Sample size {14}

Sample size calculation was performed according to the primary outcome, using an online power calculator for binary outcome non-inferiority trials (Sealed Envelope Ltd. Available from: https://www.sealedenvelope.com). This is a non-inferiority trial with a binary outcome using a one-sided alpha 0.05 and 80% power. The assumed success rate is 94.3% in the control arm, based on center-specific experience as well as the literature [14]. Data on the use of L-PRF for this indication is limited, but we assume a 95% success rate based on prior feasibility studies [8–10].

The statistical hypothesis for testing the treatment difference is presented as follows; H_0_: Δ ≤  − 0.07 tested against the alternative hypothesis H_A_: Δ >  − 0.07, where Δ is the difference between the success rates of experimental and control condition and − 0.07 is the non-inferiority difference. The non-inferiority limit was set at 0.07 considering (a) reported CSF leakage rates without commercially available fibrin sealant averaging 17.2% [15] and (b) important additional benefits of L-PRF compared to commercially available fibrin sealants including the completely autologous nature (eliminating immune reactions), presence of immunologic cells and reduced costs.

Based on this power calculation, 212 patients need to be included, 106 in each group. In order to account for potential missing follow-up information, failure of L-PRF preparation, or non-adherence to the allocation (expected drop-out rate less than 2%), 220 subjects will be enrolled, 110 in each group.

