## Statistical methods

### Statistical methods for primary and secondary outcomes {20a}

Data will be analyzed in GraphPad Prism software using a simple *t*-test, or nonparametric Mann–Whitney *U* test when not normally distributed, with Bonferroni Holm correction for multiple testing. A *p*-value ˂0.05 is considered statistically significant. The primary outcome, i.e., CSF leakage, will be analyzed in terms of a difference in risk between the two treatment groups. The mean difference between the two treatment groups will be reported as a 95% confidence interval. Secondary endpoints are calculated using simple *t*-test, or nonparametric Mann–Whitney *U* test when not normally distributed, or Fisher’s exact test or chi-squared test, based on the number of events.

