### Methods for additional analyses (e.g., subgroup analyses) {20b}

Subset analyses will be performed for surgical variables such as recurrent surgery, tumor type (hormonal balance), size, and position (Wilson-Hardy classification, Knosp classification). Demographic variables including patient age, gender, body mass index, medication use, comorbidity, and smoking habits are also analyzed. The data will be statistically tested using a simple *t*-test or Mann–Whitney *U* test, or Fisher’s exact test or chi-squared test depending on normality, type of variable, and number of events. We do not intend to perform adjusted analyses.

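### Symptom and quality-of-life scores are compared as unadjusted change from baseline; using the baseline score as a covariate would be at least as precise and needs no new data

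*Protocol article*

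**What the plan says.** Three statements in the protocol article together fix how the scores are analysed.

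- Outcomes {12}: "a comparison will be made between the two groups considering the change to baseline (preoperative visit"). The same section treats as continuous the "continuous variables (including VAS score, SBI score, SNOT-22 score").
- Statistical methods {20a}: "Secondary endpoints are calculated using simple *t*-test, or nonparametric Mann–Whitney *U* test when not normally distributed". Categorical data get Fisher's exact or chi-squared tests. A Holm correction is applied, and the software named is GraphPad Prism.
- Methods for additional analyses {20b}: "We do not intend to perform adjusted analyses".

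The baseline values are already collected. At screening, "The patient will be asked to complete nasal symptom scoring (SNOT-22, SBI, VAS scoring) and EQ-5D-3L questionnaires to assess the quality of life". Table 2 lists the same four instruments at 2 weeks, 4 weeks, 3 months and 1 year.

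The last of the three statements stands in the section on subgroup analyses. Its wording is general, though, and no other section plans any adjustment. These are stated choices, not details left open for a statistical analysis plan.

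**The concern.** A change score uses the baseline, but with a coefficient fixed at 1. An analysis of covariance (ANCOVA) estimates that coefficient from the data. Where the true slope of follow-up on baseline is not 1, the fixed coefficient leaves avoidable variation in the treatment comparison.

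Precision matters for these scores because the sample size was set for the binary CSF-leak endpoint alone. No power is stated for the questionnaires, so what the trial can say about rhinological symptoms and quality of life depends on how efficiently they are analysed. The Holm correction adds to this, since lost precision costs more at stricter thresholds.

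**Working it through.** **The plan's own figure.** Sample size {14} gives success rates of 94.3% and 95%, a margin of 0.07, one-sided alpha 0.05 and 80% power.

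n per arm = (1.645 + 0.842)² × (0.943 × 0.057 + 0.95 × 0.05) / (0.95 − 0.943 + 0.07)² = 6.18 × 0.10125 / 0.005929 ≈ 105.6, rounded up to 106, or 212 in total.

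This matches the article. It concerns the primary endpoint only and does not depend on how the scores are analysed.

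**Inputs for the scores.** The 106 per arm comes from Sample size {14}. The correlation ρ between baseline and follow-up, the baseline SD s0 and the follow-up SD s1 are not in the article. They are assumed here over a range.

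**Formulae.** Per-patient variance entering the treatment comparison (large samples):

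- change score: s0² + s1² − 2ρ·s0·s1
- baseline as covariate: s1²(1 − ρ²)
- difference between the two: (s0 − ρ·s1)²

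The difference is a square, so it cannot be negative. It is zero only when the slope ρ·s1/s0 equals 1. With equal SDs the variances are 2s²(1 − ρ) and s²(1 − ρ²), and their ratio is (1 + ρ)/2.

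**Reduction in variance from adjusting for baseline:**

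| Assumed s1/s0 | ρ = 0.3 | ρ = 0.5 | ρ = 0.7 |
|---|---|---|---|
| 1 | 1 − 0.91/1.40 = 35% | 1 − 0.75/1.00 = 25% | 1 − 0.51/0.60 = 15% |
| 1.5 | 1 − 2.0475/2.35 = 13% | 1 − 1.6875/1.75 = 4% | 1 − 1.1475/1.15 = 0.2% |
| 2 | 1 − 3.64/3.80 = 4% | 1 − 3.00/3.00 = 0% | 1 − 2.04/2.20 = 7% |

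At ρ = 0.9 with equal SDs the reduction is 5%. If the follow-up SD is smaller than the baseline SD, the reduction can exceed the equal-SD figures.

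**What the equal-SD row means in practice.** This assumes 106 per arm and a two-sided 0.05 test, and ignores the Holm correction. The smallest difference detectable with 80% power is (1.960 + 0.842) × √(2/106) × √(variance), in SD units.

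| ρ | Detectable difference, change score | Detectable difference, adjusted | Adjusted power where change score has 80% | Patients per arm for equal precision, adjusted |
|---|---|---|---|---|
| 0.3 | 0.455 | 0.367 | 93.5% | 106 × 0.65 = 68.9 |
| 0.5 | 0.385 | 0.333 | 89.9% | 106 × 0.75 = 79.5 |
| 0.7 | 0.298 | 0.275 | 86.0% | 106 × 0.85 = 90.1 |

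With equal SDs and ρ below 0.5, the change score is also noisier than the follow-up score alone (variance 1.4 against 1.0 at ρ = 0.3).

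**Simulation check.** In 4,000 simulated trials per correlation, with equal SDs and a true difference of 0.40, the variance ratios were 0.63, 0.74 and 0.87 against 0.65, 0.75 and 0.85 in theory. Both estimators averaged about 0.40, so neither is biased.

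**The case against.** The strongest reply is that the plan contains no error. Randomisation makes the change-score comparison unbiased, its standard error already allows for chance baseline differences, and no power or decision rule hangs on these scores. All of that stands. What remains is a loss of efficiency.

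The second reply is that the loss may be small. The 15 to 35% figures need equal SDs. That is doubtful here, because patients with interfering nasal disease are excluded and the baseline precedes nasal surgery, so baseline scores may vary less than early postoperative ones. This also stands, which is why the unequal-SD rows belong beside the equal-SD row. By 1 year the SD ratio could go the other way. The article does not settle it.

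A reader might infer four stronger points that the article does not support.

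- *The change score biases the result.* A chance baseline difference does carry into the comparison of the one trial that is run. Over repeated randomisations it averages to zero, and it is the same thing as the larger variance shown above.
- *Change scores over-correct unless the correlation is 1.* The slope is ρ·s1/s0. It equals 1 at ρ = 0.5 when the follow-up SD is twice the baseline SD.
- *Each visit is tested separately and patients who miss one are dropped.* Neither is stated. Section {20c} gives an imputation rule for secondary endpoints, with cost-effectiveness named in brackets, and handling of repeated visits may properly sit in a fuller document.
- *Simple randomisation makes the problem serious.* Omitting blocks mainly affects group sizes. Stratification would help only if its factors were related to the scores. With 106 per arm the standard error of a baseline difference is √(2/106) ≈ 0.14 SD.

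**Conclusion.** The point holds as one of efficiency in the secondary score comparisons. The planned analysis is valid, but it sets aside a use of the baseline scores that in large samples is never less precise and is usually more so.

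The size is uncertain: a 15 to 35% reduction in variance for correlations of 0.7 down to 0.3 with equal SDs, and about 0 to 13% if the follow-up SD is 1.5 to 2 times the baseline SD. Both the correlations and the SD ratios are assumptions. The direction of the result depends on neither. The primary CSF-leak analysis and its sample size are untouched.

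**What to change.** - In Outcomes {12} and Statistical methods {20a}, replace the unadjusted comparison of change scores. Analyse each follow-up score by ANCOVA, or by a mixed model over visits, with the baseline score as covariate. If the scores are skewed, work on a transformed or rank scale or use robust standard errors.
- Report the adjusted mean difference with its 95% CI.
- Narrow the sentence in {20b} so that it allows baseline adjustment of these scores.
- If the package named in {20a} does not fit the chosen model, name one that does.

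The cost is wording and possibly a change of software. No new data, visits or patients are needed. The change should be fixed before group allocation is released, which {17a} places after the statistical analysis.

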**Enrolment**						
Eligibility screening	X					
Informed consent	X					
Randomization		X				
**Interventions**						
Endoscopic endonasal transsphenoidal surgery		X				
Sellar floor reconstruction/closure		X				
**Assessments**						
Medical history	X					
EQ-5D	X		X	X	X	X
VAS	X		X	X	X	X
SNOT-22 questionnaire	X		X	X	X	X
SBI	X		X	X	X	X
MR imaging	X				X	X
Cost/material		X				
Intraoperative CSF leakage		X				
Nasal endoscopy to assess CSF leakage			X	X	X	X
Nasal endoscopy to assess wound healing			X	X	X	X
Nasal endoscopy to assess infection			X	X	X	X
Assessment of adverse events		X	X	X	X	X

*CSF *cerebrospinal fluid, *EQ-5D *EuroQol-5D, *SBI *Skull Base Inventory, *SNOT-22* Sino-Nasal Outcome Test with 22 items, *FU *follow-up, *VAS *visual analog scale

^a^2 weeks postoperative

^b^4 weeks postoperative

^c^3 months postoperative

^d^1 year postoperative

For the cost-effectiveness analysis, the “healthcare payer” perspective will be applied. This means that all direct treatment-related costs as well as costs related to the follow-up will be included in the analysis. In the cost analysis, the following elements will be considered: used materials during surgery (units), surgery duration (minutes), intensive care hospitalization time (days/hours), duration of hospitalization (days), associated facility and staff resources. These data will mainly be retrieved from the hospital records. The most recent unit prices at the time of analysis will be applied. Depending on the primary outcome, i.e., the effectiveness of sellar reconstruction, and the clinical effects of both treatments, either a cost-utility or a cost minimization analysis will be performed [10, 11]. In addition, the use of EQ-5D-3L to calculate QALYs at 6–12 weeks postoperative will be explored to compare EQ-5D utility scores to other outcomes described above.

### Participant timeline {13}

The participant timeline is presented in Fig. 2.

**Fig. 2 Fig2:**
[figure not shown]
Flowchart of “L-PRF in endoscopic endonasal skull base reconstruction.” After obtaining informed consent, patients are screened and asked to complete general and disease-specific quality of life (QoL) questionnaires (EQ-5D, VAS, SNOT-22, and SBI). Preoperative MR images are assessed for tumor size and location. During surgery, study subjects are randomized into experimental arm (treated with L-PRF) and control arm (commercially available fibrin sealants). Clinical follow-up visits with an endoscopic examination of the operation wound are organized at 2, 4, and 12 weeks postop. At these visits, QoL questionnaires are completed as well. MR imaging is performed at 12 weeks postop

#### Screening

At the day of hospital admission (usually 1 day before surgery), informed consent is obtained and eligibility criteria are checked. A medical history questionnaire with identification of potential risk factors for reconstruction failure and post-operative CSF leaks will be filled out. The patient will be asked to complete nasal symptom scoring (SNOT-22, SBI, VAS scoring) and EQ-5D-3L questionnaires to assess the quality of life. Pre-operative MR images will be evaluated.

#### Randomization

The EETA will be performed according to local standards. During surgery, patients are randomized into experimental (L-PRF) and control (commercially available fibrin sealant) groups. Defects after closure and the need for muscle or fascia grafts are recorded. Visible perioperative CSF leakage and other complications are assessed. For each surgery, all used materials are registered and exact costs will be calculated.

#### Outpatient follow-up

The patient is seen at the outpatient clinic at four occasions to evaluate the postoperative status: after 2 weeks, 4 weeks, 3 months, and 1 year. At each of these visits, a nasal endoscopy is performed to evaluate healing using the Ohio State University crusting scale from 0 to 3 (Table 3). Signs and symptoms of CSF leakage or fistula formation will be recorded. The patient will be asked to complete nasal symptom scoring (SNOT-22, SBI, VAS scoring) and EQ-5D-3L questionnaires to assess the quality of life. At FU3 and FU4, post-operative MR images will be evaluated as well.

**Table 3 Tab3:** Ohio State University crusting scale

Crusting	
0	No crusting
1	Minimal crusting debrided with suction only
2	Moderate crusting (coating) requiring forceps debridement
3	Severe crusting (casting) causing obstruction

FU1 is an additional study visit, which is not part of the standard of care.

### Sample size {14}

Sample size calculation was performed according to the primary outcome, using an online power calculator for binary outcome non-inferiority trials (Sealed Envelope Ltd. Available from: https://www.sealedenvelope.com). This is a non-inferiority trial with a binary outcome using a one-sided alpha 0.05 and 80% power. The assumed success rate is 94.3% in the control arm, based on center-specific experience as well as the literature [14]. Data on the use of L-PRF for this indication is limited, but we assume a 95% success rate based on prior feasibility studies [8–10].

The statistical hypothesis for testing the treatment difference is presented as follows; H_0_: Δ ≤  − 0.07 tested against the alternative hypothesis H_A_: Δ >  − 0.07, where Δ is the difference between the success rates of experimental and control condition and − 0.07 is the non-inferiority difference. The non-inferiority limit was set at 0.07 considering (a) reported CSF leakage rates without commercially available fibrin sealant averaging 17.2% [15] and (b) important additional benefits of L-PRF compared to commercially available fibrin sealants including the completely autologous nature (eliminating immune reactions), presence of immunologic cells and reduced costs.

Based on this power calculation, 212 patients need to be included, 106 in each group. In order to account for potential missing follow-up information, failure of L-PRF preparation, or non-adherence to the allocation (expected drop-out rate less than 2%), 220 subjects will be enrolled, 110 in each group.

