**Methods/design:**

This multicenter, prospective randomized controlled trial aims to demonstrate non-inferiority of L-PRF membranes compared to commercially available fibrin sealants in EETA cases (1) without intra-operative CSF-leak as dural or sellar floor closure reinforcement and (2) in EETA cases with intra-operative CSF-leak (or very large defects) in which a classic multilayer reconstruction has been made, as an additional sealing. The trial includes patients undergoing EETA in three different centers in Belgium. Patients are randomized in a 1:1 fashion comparing L-PRF with commercially available fibrin sealants. The primary endpoint is postoperative CSF leakage. Secondary endpoints are identification of risk factors for reconstruction failure, assessment of rhinological symptoms, and interference with postoperative imaging. Additionally, a cost-effectiveness analysis is performed.

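### The trial is sized for a one-sided 5% test, but the only interval planned for the primary difference is a 95% one and no bound is named for the comparison with -0.07; if the 95% interval decides, power is about 70%, not 80%

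*Protocol article*

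**What the plan says.** Sample size {14} sets the design level: "This is a non-inferiority trial with a binary outcome using a one-sided alpha 0.05 and 80% power". It gives the null hypothesis as a success-rate difference (L-PRF minus control) of -0.07 or less, against the alternative that it is greater than -0.07. Its inputs are:

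- Control: "The assumed success rate is 94.3% in the control arm".
- L-PRF: "we assume a 95% success rate based on prior feasibility studies".
- Result: "212 patients need to be included, 106 in each group", raised to 110 per group for enrolment.

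Statistical methods {20a} says the primary outcome is analysed as a difference in risk, and then: "The mean difference between the two treatment groups will be reported as a 95% confidence interval". Its only other criterion is a p-value threshold of 0.05, with no sidedness given. That section mentions neither the margin, nor a one-sided bound, nor a 90% interval. Outcomes {12} also uses 95% intervals, for the success rate in each arm.

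**The concern.** A non-inferiority conclusion is usually read from a confidence limit set against the margin. A one-sided 5% test corresponds to the lower limit of a two-sided 90% interval. The lower limit of a two-sided 95% interval is a one-sided 2.5% test. The article sizes the trial for the first and, in its analysis section, plans an interval that delivers the second. No sentence connects the two.

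An analyst who works from the statistical methods section alone would naturally set the 95% interval against -0.07 and so apply a stricter test than the one the trial was powered for. An analyst who works from the sample size section would use the 90% limit. The trial's main claim depends on this comparison. About six leaks per arm are expected, so the two limits can fall on opposite sides of the margin for quite ordinary results.

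**Working it through.** **Inputs** (Sample size {14}): control success 0.943, L-PRF success 0.95, margin 0.07, one-sided alpha 0.05, power 0.80. Allocation is 1:1 (abstract, Methods/design).

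**1. Reproduce the stated size** (normal approximation, unpooled variance).

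n per arm = (z_alpha + z_beta)² × [pC(1 − pC) + pT(1 − pT)] / (margin + pT − pC)²

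- Variance sum: 0.943 × 0.057 + 0.95 × 0.05 = 0.05375 + 0.04750 = 0.10125
- Denominator: (0.07 + 0.007)² = 0.077² = 0.005929
- One-sided 0.05: (1.645 + 0.842)² × 0.10125 / 0.005929 = 105.6, so 106 per arm and 212 in total. This matches the article.
- One-sided 0.025: (1.960 + 0.842)² × 0.10125 / 0.005929 = 134.04, so 135 per arm and 270 in total.

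The sizing level is therefore not in doubt: 106 belongs to one-sided 5%.

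**2. Power at the planned size.**

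Power = Φ(0.077 / √(0.10125 / n) − z_alpha)

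| n per arm | 0.077 / SE | one-sided 5% (90% interval) | one-sided 2.5% (95% interval) |
|---|---|---|---|
| 106 | 2.491 | Φ(0.847) = 80.1% | Φ(0.531) = 70.2% |
| 110, all evaluable | 2.538 | Φ(0.893) = 81.4% | Φ(0.578) = 71.8% |

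**3. Dependence on the interval method.** The article names no method. Exact binomial enumeration under the same rates gives:

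| n per arm | Wald 90% | Wald 95% | Newcombe 90% | Newcombe 95% |
|---|---|---|---|---|
| 106 | 80.2% | 71.5% | 76.1% | 63.7% |
| 110 | 81.8% | 72.7% | 78.4% | 67.1% |

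A trial that passes at the 95% limit also passes at the 90% limit. The gap between the Wald columns is therefore the chance that the two readings disagree: 80.2 − 71.5 = 8.7 points at 106 per arm, and 81.8 − 72.7 = 9.1 points at 110.

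**4. A concrete result.** Take 110 per arm with 7 leaks on L-PRF and 6 on control. The design expects 110 × 0.05 = 5.5 and 110 × 0.057 = 6.3.

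- Difference in success: 103/110 − 104/110 = −0.0091
- SE = √[(0.9364 × 0.0636 + 0.9455 × 0.0545) / 110] = 0.0318
- Lower 90% limit: −0.0091 − 1.645 × 0.0318 = −0.061, above −0.07, so non-inferiority is met
- Lower 95% limit: −0.0091 − 1.960 × 0.0318 = −0.071, below −0.07, so it is not met

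**The case against.** The strongest reply is that the test is already fixed. Sample size {14} states the hypotheses, direction, margin and one-sided 5% level, and the statistical methods section says only that the 95% interval will be reported, not that it decides. A one-sided 5% test shown beside a conventional 95% interval is not in itself a contradiction, and neither 2.5% nor two-sided appears anywhere in the article. It can be added that the choice of bound is often left to an analysis plan, which is not shown here.

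Much of this stands, and it rules out several stronger readings that a reader might infer:

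- *That 212 patients or 80% power is a miscalculation.* Both reproduce from the stated inputs.
- *That the trial simply has 70% power.* That holds only if the 95% interval decides, and the article does not say that it does.
- *That the level is free to be chosen after the result.* Using 2.5% would depart from the level stated in the sample size section.
- *That assuming 95% for L-PRF against 94.3% for control is an error.* The assumption is disclosed, its limited basis is admitted, and a small expected advantage is permissible in sizing a non-inferiority trial. Power at equal rates of 94.3% (about 71% at one-sided 5% with 106 per arm) is a useful sensitivity figure, but optional.

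What the reply does not remove is the gap between the two sections. The point does not rest on the article's silence: it states one error level for sizing, plans an interval at another for the same difference, and identifies no other interval for the decision. An analysis plan that adopted the 95% interval would conflict with the stated power. One that adopted the 90% interval would have to add something the article's analysis text does not contain.

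**Conclusion.** The concern holds as an inconsistency between the sizing and the analysis text, not as an arithmetic error. If the planned 95% interval is set against -0.07, power falls by about 10 points, from 80.1% to 70.2% at 106 per arm (81.4% to 71.8% at 110). Under the design assumptions the two readings would disagree in about 9% of trials with Wald limits.

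These figures assume that the 95% interval is two-sided, that the true rates are 94.3% and 95%, and, for the 70% and 72%, the normal approximation. A Newcombe 95% interval gives 63.7% and 67.1%. If a one-sided 95% bound decides, the stated 80% stands as calculated and the 95% interval is only descriptive.

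It should be corrected, because it concerns the rule for the primary conclusion and the correction is small.

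**What to change.** Settle one level in both sections, before unblinding. Either of these would do:

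1. **Keep the stated design.** Add to Statistical methods {20a} that non-inferiority is concluded when the lower limit of the two-sided 90% interval (the one-sided 95% bound) for the success-rate difference, L-PRF minus control, exceeds -0.07, and that the 95% interval is descriptive. The stated alpha, sample size and power are unchanged.
2. **Let the 95% interval decide.** Say so in {20a}, change alpha in Sample size {14} to one-sided 0.025, and restate the power as about 70% at 106 per arm, recalculated for the interval method chosen.

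In either case name the interval method, since Wald and Newcombe limits differ by several points of power at this size. Power under equal success rates may be added as a sensitivity figure.

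The cost is a sentence or two in an amendment, with no extra patients and no change in conduct. Under the second option the stated power becomes less favourable.

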### Trial design {8}

This study is a multicenter, single-blinded, prospective randomized controlled trial with subjects randomized 1:1 in two parallel groups, i.e., experimental (L-PRF treatment) and active control (commercially available fibrin sealants).

In this study, the general objective is to show non-inferiority of L-PRF as a closure technique compared to commercially available fibrin sealants in endoscopic transsphenoidal surgery. This prospective randomized controlled trial was approved by the local Ethical Committee (UZ Leuven (S61636), AZ Sint-Jan Brugge, UZ Gent) and is registered at ClinicalTrials.gov (ID: NCT003910374). Recruitment started on 07 November 2018.

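### With 5 to 6 expected leaks per arm, the normal-approximation sample size does not deliver one-sided 5% error and 80% power together; a score limit that holds 5% has about 76% power

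*Protocol article*

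**What the plan says.** Sample size {14} gives all design inputs. The error rate and power are "This is a non-inferiority trial with a binary outcome using a one-sided alpha 0.05 and 80% power". For the control arm, "The assumed success rate is 94.3% in the control arm"; for L-PRF, "we assume a 95% success rate based on prior feasibility studies". The hypothesis is on the risk-difference scale, where Δ "is the difference between the success rates of experimental and control condition and − 0.07 is the non-inferiority difference". The result is "Based on this power calculation, 212 patients need to be included, 106 in each group", with 220 enrolled (110 per arm) to cover an expected loss below 2%. The section cites an online calculator for binary non-inferiority trials.

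Statistical methods for primary and secondary outcomes {20a} says that CSF leakage is analysed as a difference in risk, and that "The mean difference between the two treatment groups will be reported as a 95% confidence interval". It names no way of constructing that interval (Wald, score, Newcombe or other) and does not mention a 90% interval.

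**The concern.** The calculation treats the estimated risk difference as normal, with a variance computed from the assumed success rates. That works when both outcomes are reasonably frequent. Here failures are rare, and the limit is compared with a margin of 7 points when the control leak rate itself is only 5.7%. In that region a simple limit tends to be too optimistic: it declares non-inferiority more often than its nominal level allows when L-PRF is truly 7 points worse. The excess favours the experimental arm, and it grows as leaks become rarer. The Background section cites a 4.1% average leak rate, below the planning value, so that direction is plausible. A limit that holds its level pays for it in power.

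At stake is whether the stated pair of 5% and 80% describes what the trial will do, and whether the interval is fixed before a borderline result could make the choice of method decisive.

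**Working it through.** **Inputs** (all from Sample size {14} unless noted): control success 0.943 (leak 0.057); L-PRF success 0.95 (leak 0.05); margin 0.07; one-sided α = 0.05; power 0.80; 106 per arm required, 110 enrolled; 1:1 allocation (Trial design {8}). The 4.1% leak rate is from Background and rationale {6a}.

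**Step 1: reproduce the plan's figure.** Unpooled normal formula:

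n = (z₀.₉₅ + z₀.₈₀)² × [p_C(1−p_C) + p_T(1−p_T)] / (p_T − p_C + 0.07)²

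= (1.645 + 0.842)² × (0.943 × 0.057 + 0.95 × 0.05) / (0.007 + 0.07)²

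= 6.183 × 0.10125 / 0.005929 = 105.6, so 106 per arm and 212 in total. The stated number is reproduced, with approximate power of 80.1% at 106.

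**Step 2: expected events.** 106 × 0.057 = 6.0 leaks on control; 106 × 0.05 = 5.3 on L-PRF.

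**Step 3: exact operating characteristics.** For each pair of success counts (x_T, x_C) from 0 to n, mark whether the lower limit for p_T − p_C exceeds −0.07. Then sum the product of the two binomial probabilities over the marked pairs:

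- true error: p_C = 0.943, p_T = 0.943 − 0.07 = 0.873;
- power: p_C = 0.943, p_T = 0.95.

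Nominal one-sided 5%:

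| Limit | n per arm | True error | Power |
|---|---|---|---|
| Simple (Wald) | 106 | 5.65% | 80.2% |
| Score | 106 | 4.82% | 76.1% |
| Newcombe | 106 | 4.8% | 76.1% |
| Simple (Wald) | 110 | 5.83% | 81.8% |
| Score | 110 | 4.88% | 76.5% |
| Newcombe | 110 | 4.96% | 78.4% |
| Agresti-Caffo | 110 | 4.97% | 79.2% |

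At 106 per arm the *t*-based and pooled-variance versions of the simple limit give the same 5.65%. Agresti-Caffo at 106 has a true error of 5.4%, so it does not hold the level there.

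**Step 4: sensitivity to the control leak rate.** At 106 per arm the true error of the simple limit is 5.3% at a 10% leak rate, 5.65% at 5.7%, 6.0% at 4.1% and 6.6% at 3%. The score limit stays between 4.5% and 5.1% for control success from 0.86 to 0.99.

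**Step 5: the 95% interval of section {20a}.** Its lower bound is a nominal one-sided 2.5% limit.

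| Limit | n per arm | True error | Power |
|---|---|---|---|
| Simple (Wald) | 106 | 3.1% | 71.5% |
| Score | 106 | 2.4% | 63.7% |
| Score | 110 | 2.3% | 63.2% |

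**Step 6: size at which a score limit reaches 80%.** At one-sided 5%, exact power is 79.9% at 117 per arm and 80.4% at 118 (236 evaluable), above the 220 to be enrolled.

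**The case against.** There are four fair objections.

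*The sample size contains no error.* This stands. The inputs return 106, and a nominal α and a formula-based power are what such a section normally reports. The gap is approximation error with few events, not a slip in arithmetic.

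*The 5.7% belongs to an interval that the protocol does not name.* This also stands. A reader might infer that the planned interval has a 5.7% error. The documents do not support that: 5.65% is the error of the lower bound of a simple 90% interval, whereas the interval named is 95%. If that interval is simple, its true error of 3.1% lies below the 5% of the sample-size section, though above its own nominal 2.5%. The mismatch between one-sided 5% and a 95% interval is a separate issue and costs more power than the one described here.

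*No Wald rule is stated.* Correct. The mean-difference wording and the surrounding *t*-tests hint at a simple interval but do not establish one, and an analysis plan that is not shown may name the construction. That limits what can be said about error. It matters less for power: a score limit named elsewhere would still have about 76% at one-sided 5%.

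*The shortfall depends on the method.* True. At 110 per arm, Newcombe (78.4%) and Agresti-Caffo (79.2%) come within one to two points of 80% with about 5% error at the planning rates. The loss is therefore roughly 1 to 4 points, not a fixed four. It is also small beside the uncertainty in the assumed 95% L-PRF rate, for which the protocol itself says that data are limited.

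**Conclusion.** The point holds in a limited form. At 106 per arm and the plan's own rates, none of the simple, score, Newcombe or Agresti-Caffo limits gives both a true one-sided error of at most 5% and 80% power. The simple limit keeps the power and exceeds 5% by about 0.65 points in favour of L-PRF. The score limit keeps the level and loses about 4 points of power. A simple limit exceeds its nominal level at 2.5% as well (3.1%).

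The figures assume equal arms of exactly 106 or 110, complete primary outcome data, and true success rates of 94.3% and 95%. Severity is low: the effect is modest, and the correction is a matter of wording.

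**What to change.** In Statistical methods {20a}, specify that non-inferiority is judged by the Miettinen-Nurminen (Farrington-Manning) score lower limit for the risk difference in success, at the one-sided level that the trial adopts, compared with −0.07.

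In Sample size {14}, describe 80% as the normal-approximation figure. Add that exact power with the score limit is about 76% at one-sided 5% with 106 to 110 evaluable per arm, or about 63–64% if the lower bound of the 95% interval decides.

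The cost is two amended sentences and a less favourable stated power. No patients are added. Restoring 80% exact power with a score limit at one-sided 5% would need about 118 evaluable per arm; the correction proposed here does not require that.
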